## Abstract

**Background:**

Knee osteoarthritis (KOA) is a major public health issue causing chronic disability as well as a burden on healthcare resources. In China, a herbal drug tablet has been used as an effective and conventional therapy to alleviate clinical symptoms caused by KOA. However, evidence gathered from systematic reviews or randomized controlled trials that validated herbal drugs for the management of osteoarthritic pain is weak. The purpose of this study is to explore the efficacy and safety of the *Shaoyao Shujin* tablet for the management of KOA in a short-term study.

**Methods/Design:**

This trial is a multicenter randomized, double-blind, placebo-controlled study. A total of 276 patients will be randomized into 3 groups: (1) the high-dose *Shaoyao Shujin* tablet group (HD group), (2) the low-dose *Shaoyao Shujin* tablet group (LD group), and (3) the placebo tablet group (control group). In the three groups, four tablets will be administered three times per day for 6 weeks. Follow-up will be at regular intervals during a 10-week period with the Western Ontario and McMaster Universities Index (WOMAC) score, visual analog scale (VAS) score, and rescue medication use assessed as outcome measures.

**Discussion:**

This study will provide clinical evidence on the efficacy and safety of the *Shaoyao Shujin* tablet in treating KOA.

**Trial registration:**

Chinese Cochrane Center ChiCTR-IPR-15006194, registered 4 April 2015.

## Background

Knee osteoarthritis (KOA) is a prevalent disease causing disability in the aging population. The risk of KOA disability, characterized as chronic pain and functional limitation, is as great as that attributable to cardiovascular disease and greater than that due to any other medical condition in older persons [1]. In the US, estimated average discounted (3 % per year) lifetime costs for persons diagnosed with KOA were US$140,300, and direct medical costs were US$129,600, with US$12,400 (10 %) attributable to KOA over 28 years [2]. Determining effective means of treating KOA has become an important subject of study, particularly because currently there is no medical treatment to reverse or stop its progression. Pharmacological approaches include analgesics, anti-inflammatory agents, corticosteroids given by the intra-articular route, or hyaluronic acid, glucosamine sulfate, and chondroitin sulfate, which are already widely use. However, these drugs have some adverse effects such as constipation, nausea, and excessive sedation in older people, and their effect on cartilage with OA changes remains controversial [3–5].

The aim of KOA treatment is to reduce pain, improve physical function, prevent disability, and enhance short-term quality of life. The herbal drug the *Shaoyao Shujin* tablet (SST, previously called *Yangxue ruanjian jiaonang*) is a multicomponent Chinese herbal supplement that has been proved to be an effective regimen to relieve KOA pain in patients [6] or to delay the degeneration of articular cartilage in KOA animal models [7, 8]. However, understanding of the mechanisms responsible for the beneficial effects of SST is limited and its clinical effectiveness needs strong evidence for proof. Published Chinese medical literature has documented that SST is efficacious in treating KOA, but these interventions have not been rigorously evaluated, and their credibility questioned, due to a lack of objective evidence [9]. Therefore, we designed a multicenter randomized, double-blind, placebo-controlled trial to explore the efficacy and safety of SST for the symptomatic management of KOA in a short-term study.

## Methods/Design

### Study design

This is a multicenter randomized, double-blind, placebo-controlled trial. General ethical approval was issued by the Ethics Committee of Guangdong Provincial Hospital of Chinese Medicine (No. A2015-01-2-1), and participating center ethical approval was issued by the Clinical Trial Ethics Committee of Huazhong University of Science and Technology (No. FZ-1302-01), the Ethics Committee of The First Affiliated Hospital of Anhui University of TCM (No. 2015AH-03), the Clinical Trial Ethics Committee of The First Affiliated Hospital of Hunan University of TCM (No. 2015-YW-001), and the Ethics Committee of Shanghai Hospital of TCM (No. 2015SHL-05). Subjects will be enrolled at these five hospitals. The trial protocol has been registered in the Chinese Clinical Trial Registry (ChiCTR-IPR-15006194). All study participants will sign the written informed consent before participation. The trial is financially supported by Shanghai Fosun Pharmaceutical Development Co., Ltd, Shanghai, China, which will participate in the study design, but will not be involved in data collection, data management, analysis, interpretation of data or the decision to submit the report for publication, but will provide all test drugs.

### Recruitment and consent

A target sample size of 276 KOA patients, who are regularly followed up at outpatient clinics of the Department of Orthopedic Surgery in each participating center, will be recruited. All candidates will go through a standardized interview process and receive more information about the study and the treatments. The purpose, procedures, and potential risks and benefits of the study will also be explained thoroughly to the participants. The more painful knee will be chosen as the study knee, and if both knees have the same symptoms, we will choose the right side. The participants will be able to withdraw from the study at any time without consequence. The trial will be executed from February 2015 to February 2016 including enrollment and follow-up (see Fig. 1).

**Fig. 1 Fig1:**
[figure not shown]
Study flow-chart

### Inclusion criteria

Participants meeting the following criteria will be included:Meet the diagnostic criteria for KOA (American College of Rheumatology criteria [10])Aged from 40 to 70 years oldSymptomatic KOA with pain of at least 30 mm on a 100-mm visual analog scale (VAS)Grade 0–3 on the Kellgren-Lawrence grading systemNo serious medical historyNo known drug allergiesWillingness to give written informed consent and willingness to participate in, and comply with, the study

### Exclusion criteria

Participants meeting one or more of the following criteria will be excluded:Grade 4 on the Kellgren-Lawrence grading systemMedication history for KOA within 1 week, such as NSAIDs, steroids, glucosamine, chondroitin sulfate, sodium hyaluronate, etc.Allergy to study drugNon-degenerative osteoarthritis, such as rheumatoid arthritis, gouty arthritis, infectious arthritis, Charcot arthritis, etc.Unwilling to give informed consent

### Interventions

Eligible patients will be randomized into the three groups: (1) the high-dose SST group (HD group), (2) the low-dose SST group (LD group), and (3) the placebo tablet group (control group). The SST will be provided by the Shanghai Fosun Pharmaceutical (Group) Co., Ltd, Shanghai, China (drug permit license number 2014L00464) and weighs 0.35 g per tablet. The components of the SST are *Radix paeoniae alba*, *Radix Gentianae Macrophyllae*, oyster, licorice, scorpion, and centipede. The placebo tablet will be manufactured identical to the SST in terms of color and odor by the same manufacturer. In the HD group four SSTs will be administered three times per day for 6 weeks, while in the LD group two SSTs and two placebo tablets, and in the control group four placebo tablets at the same frequency and for the same duration. Patient visits will be performed at baseline and 2, 4, 6 and 10 weeks after treatment. Assessments including the Western Ontario and McMaster Universities Index (WOMAC) score and the VAS score will be recorded on the relevant knee during all visits.

As a short-term study aims to explore the efficacy and safety of SST for the symptomatic management of KOA, we think that 6 weeks’ treatment and 4 weeks’ follow-up will be enough to observe whether there are differences between the HD group, the LD group and the placebo tablet group.

During the process, when patients experience moderate pain or a VAS score over 40 mm, ibuprofen sustained-release capsules will be administrated as rescue medication. Rescue medication consumption and time will be recorded in each randomized group when the subjects use rescue medication. The patients will not be allowed to use other drugs aiming to treat KOA.

### Outcome measures

#### Primary outcome measure

The primary efficacy endpoint of the study will be the WOMAC score [11]. The WOMAC score is a widely used proprietary set of standardized questionnaires used by health professionals to evaluate the condition of patients with osteoarthritis of the knee and hip, including pain, stiffness, and physical functioning of the joints. The index measures five items for pain (score range 0 to 20), two for stiffness (score range 0 to 8), and 17 for physical function (score range 0 to 68). It will be measured during all the assessment visits (baseline, 2-, 4-, 6- and 10-week follow-up).

#### Secondary outcome measure

The secondary efficacy endpoint of the study will be the VAS score, which is a pain score ranging from 0 mm (no pain) to 100 mm (worst pain ever experienced) [12], measured during all the assessment visits (baseline, 2-, 4-, 6- and 10-week follow-up). The VAS score is usually a horizontal line, 100 mm in length, anchored by word descriptors at each end. Patients mark the point of their current pain on the line. The VAS score is then determined by measuring in millimeters from the left end of the line to the point that the patient marked.

### Safety assessments

All subjects will be questioned about adverse events during the treatment at each visit, and all adverse events reported will be analyzed, regardless of the investigators’ assessments of causality. Safety will be assessed by the following tests on all subjects: physical examination (temperature, respiration, heart rate, blood pressure, height and weight), complete blood cell count, urinalysis, stool examination, fecal occult blood test, liver function (alanine aminotransferase (ALT), aspartate aminotransferase (AST), alkaline phosphatase (ALP), serum total bilirubin (STB), and γ-glutamyl transpeptidase (γ-GT)), renal function (creatinine (Cr), micro-albuminuria, serum cystatin C, and urinary *N*-acetyl-β-glucosaminidase) and an electrocardiogram (ECG) at baseline and at 2- and 6-week visits.

### Randomization and blinding

Patients who meet the inclusion criteria will be randomly assigned to one of three groups (HD group, LD group, control group) in a ratio of 1:1:1 using a computer-generated random allocation sequence through the stratified block randomization method of SAS version 9.1.3 (SAS Institute Inc., Cary, NC, USA). Each patient will receive a unique randomized test number corresponding to the specified drug, according to the group allocation. An emergency envelope has been prepared for each test number and is to be opened.

The trial will be blinded to both patients and treating physicians. For test drug blinding, the placebo tablet will be manufactured identical to the SST in terms of color and odor. The drugs are administered by an independent clinical assistant in each center who takes responsibility for the drugs’ distribution, storage and return. Any members who have access to the drug will not participate in case observations or efficacy evaluations. Before the trial two different bottles will be prepared: bottle A contains a 2-week dose of SSTs and bottle B contains a 2-week dose of placebo tablets. Bottles A and B will be packaged with the same label for patient and assessor blinding. For the HD group, two A bottles will be assigned; for the LD group, one A bottle and one B bottle will be assigned; and for the control group, two B bottles will be assigned. During baseline, and 2-, and 4-week visits, patients will be assigned two bottles according to their group, and 14 rescue medications. They will then be instructed to take two tablets from each bottle every time they take their drugs. At the next visit, the patient should return all the rescue medications they didn't taken.

### Sample size

Calculation of sample size is based on a similar herbal drug study assessing the short-term efficacy of two types of Traditional Chinese herbal patches, *Fufang Nanxing Zhitong Gao* and *Shangshi Jietong Gao* [13]. We estimate that an absolute improvement of 10 in the WOMAC total score is likely to be the smallest clinically relevant difference for patients with KOA. We assume that the standard deviation of the total WOMAC score to be 18.2 at baseline. Based on these assumptions, we will require 79 patients in each group to have at least an 80 % power (*β* = 0.8) and to rule out a two-sided type I error of 5 % (*α* = 0.05). The number of patients actually provides less than 80 % power, assuming a withdrawal rate of 15 %. Therefore, we will recruit a total of 276 patients, 92 patients in each group.

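### The printed sample-size inputs give 53 patients per group for one pairwise comparison, not 79; the input behind 79 is not stated

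*Protocol article*

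**What the plan says.** The Sample size section of the protocol article sets out a complete chain.

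- Difference: an "absolute improvement of 10 in the WOMAC total score is likely to be the smallest clinically relevant difference".
- Spread: "We assume that the standard deviation of the total WOMAC score to be 18.2 at baseline".
- Error rates: the trial is "to have at least an 80 % power", with β printed as 0.8, and to "rule out a two-sided type I error of 5" %.
- Result: "Based on these assumptions, we will require 79 patients in each group".
- Withdrawal: "The number of patients actually provides less than" 80 % power once 15 % withdrawal is assumed.
- Final number: "Therefore, we will recruit a total of 276 patients, 92 patients in each group".

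The Randomization and blinding section gives three arms in a 1:1:1 ratio. The Statistical analysis section repeats a two-sided 0.05 level. The article states no second SD, change-score SD, baseline correlation, multiplicity rule or definition of power over more than one comparison.

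**The concern.** The paragraph prints every input that a comparison of two means needs and says that the result rests on them. The standard formula gives a much smaller number. The sentence that justifies raising 79 to 92 makes a second power claim that also fails on the same inputs. At stake is whether the printed justification is the one used. If the real calculation had a larger SD, or required both doses to succeed, the trial's margin is much thinner than the printed inputs suggest. A reader cannot tell which case applies.

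**Working it through.** **Inputs** (Sample size section): difference δ = 10, SD σ = 18.2, two-sided α = 0.05, power 0.80, withdrawal 15 %. Equal allocation is from Randomization and blinding.

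**1. Attempt to reproduce 79.** Normal approximation:

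n = 2(1.960 + 0.842)² × 18.2² / 10² = 52.0 per group.

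The exact t-test solution is 52.97, so 53. The printed 79 is 79/53 = 1.49 times this.

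**2. Power for one pairwise comparison at the printed sizes.** Noncentrality = 10 / (18.2 × √(2/n)); power ≈ Φ(noncentrality − 1.960).

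| n per group | Noncentrality | Power, normal | Power, t-test |
|---|---|---|---|
| 79 | 3.453 | 93.2 % | 93.0 % |
| 67 (79 × 0.85 = 67.15) | 3.180 | 88.9 % | 88.4 % |
| 78 (92 × 0.85 = 78.2) | 3.431 | 92.9 % | 92.6 % |

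At 78 per group the t-test power is about 88 % at α = 0.025 and 84 % at α = 0.05/3.

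**3. Common variants with δ = 10 and σ = 18.2.**

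| Variant | n per group |
|---|---|
| 85 % power, α 0.05 | 60–61 |
| 90 % power, α 0.05 | 70–71 |
| 95 % power, α 0.05 | 87–88 |
| 80 % power, α 0.05/2 | 63–65 |
| 80 % power, α 0.05/3 | 70–71 |
| Three-group ANOVA, 80 % power | 49–65, depending on the pattern of means |
| Rank test, 80 % power | 55–62 |

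None gives 79.

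**4. What does give 79.** Each route needs something the article does not print, or contradicts something it does.

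- A larger SD: 80 % power at 79 per group by t-test needs σ of about 22.3 (22.4 by the normal formula). A change-score SD of that size follows from 18.2 × √(2(1 − ρ)) with ρ of about 0.25.
- Both doses superior to placebo: δ = 10 for each dose, σ = 18.2, pairwise t-tests sharing the placebo arm, 0.025 for each comparison. Power to succeed on both is 79.8 % at n = 78, 80.5 % at n = 79 and 71 % at n = 67.
- Two-sided α = 0.01 (78–80), or 85 % power at α = 0.05/3 (78–80). These conflict with the printed 5 % level or 80 % power.

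The first two routes would also make the withdrawal sentence true. With σ = 22.3 and n = 67, the noncentrality is 10 / (22.3 × √(2/67)) = 2.60, and Φ(2.60 − 1.96) is about 74 %.

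**5. The step from 79 to 276.** 79/0.85 = 92.9, which rounds up to 93 (279 in total). The article uses 92, and 92 × 3 = 276. That leaves about 78 evaluable per group, one short of the stated 79.

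**6. Label.** Power is 1 − β, so 80 % power is β = 0.2, not 0.8.

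**The case against.** The strongest reply is that this is a three-arm trial and the check uses a two-group formula. Requiring both doses to beat placebo at 0.025 each keeps the printed difference, SD, 80 % power and overall 5 % level. It gives exactly 79, and it makes the withdrawal sentence correct. This stands in part. The article does not describe that construction and the match may be coincidence, but it is a reason not to call 79 or the withdrawal sentence false outright. What can be said is that neither follows from the assumptions as printed.

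A related reply is that the article condenses a fuller protocol and bases its calculation on a cited patch study, so an input may have been dropped. That may explain the gap. It does not repair a sentence that attributes 79 to the assumptions just listed.

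Several stronger readings are tempting, and the document does not support them.

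- *The claim of at least 80 % power is wrong.* It is not: 79 per group gives about 93 % on the printed inputs. What fails is that 79 are required.
- *The trial over-enrols by 87.* That figure comes from 53/0.85 = 62.4, so 63 per group, 189 in total, and 276 − 189 = 87. It holds only for one unadjusted comparison. With 53 per group, power to show both doses superior is about 69 % at 0.05 each and 57 % at 0.025 each.
- *A null result could not be interpreted.* The confidence interval can still be read against the printed 10-point difference.
- *The origin of 276 is unknown.* The step from 79 to 276 can be traced; only the basis of 79 is missing.

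**Conclusion.** The point holds as a failure of the printed justification. For one dose-versus-placebo comparison the stated inputs need 53 per group against the stated 79. Power is about 93 % at 79 and about 88 % at 67, so neither the requirement for 79 nor the drop below 80 % follows from what is printed. These figures assume a two-sided two-sample t-test with σ = 18.2 in each group. Which unstated input lies behind 79, if any, cannot be settled from the article.

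The choice matters for the margin. On the printed inputs, about 78 evaluable per group give roughly 93 % power for a single comparison. If the working SD was about 22.3, the same 78 give just under 80 % (79.5 %), with nothing in reserve for a second dose comparison. The β label is a plain misprint, and the rounding to 92 is a shortfall of one evaluable patient per group.

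**What to change.** Keep 276 and rewrite the paragraph.

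1. State the input that gives 79: the SD or change-score SD with its correlation, the multiplicity rule, or the definition of power over the two dose comparisons. Keep the sentence about falling below 80 % only if that input supports it.
2. If there is no such input, say that 53 evaluable patients per group give 80 % power for a single dose-versus-placebo comparison (difference 10, SD 18.2, two-sided 0.05). Say also that 92 randomised per group, about 78 evaluable after 15 % withdrawal, give about 93 % at 0.05, 88 % at 0.025 or 84 % at 0.05/3. Remove the sentence about falling below 80 %.
3. In either case, correct β to 0.2. If 79 is kept as the evaluable target, note that 92 per group leaves about 78.

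The cost is one paragraph of text, with no change in enrolment or conduct.

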### Statistical analysis

The data will be collected and analyzed according to the intention-to-treat principle. An analysis of variance (ANOVA) or chi-square test will be used to compare baselines among patients. Efficacy analyses will be performed for both the intent-to-treat (ITT) population and the per-protocol (PP) population. The ITT population will consist of all randomized subjects who have been administered at least one treatment. In a PP analysis, only patients who complete the entire clinical trial according to the protocol are counted towards the final results. Primary outcome will be compared among groups; the extent and time pattern of rescue medication use in each randomized group will be reported: in considering comparison of the underlying outcomes of rescue medication use, we will assume the use varies with time and, to allow for dependence within patients, we will adopt a multilevel regression approach with rescue as a time-dependent covariate [14]. All statistical analyses will be performed using SAS 9.2 software. All statistical tests will be two-sided, and the level of significance will be set at 0.05.

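### The stated 5 % type I error is not secured across two doses and a placebo: two dose-placebo tests at 0.05 each, as the blanket rule permits, give about 9.1 %

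*Protocol article*

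**What the plan says.** The Randomization and blinding section assigns patients to "one of three groups (HD group, LD group, control group) in a ratio of 1:1:1". The Interventions section says the treatment and follow-up periods should be long enough to "observe whether there are differences between the HD group, the LD group and the placebo tablet group". No contrast among the three arms is given priority.

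The Sample size section states that "we will require 79 patients in each group to have at least an 80 % power" and "to rule out a two-sided type I error of" 5 %. Its inputs are a 10-point difference in WOMAC total and an SD of 18.2. With 15 % withdrawal, this leads to 92 patients per group, 276 in all.

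On the analysis of the primary outcome, the Statistical analysis section says only: "Primary outcome will be compared among groups". ANOVA is named there, but for baseline comparisons. The section closes with the general rule "All statistical tests will be two-sided, and the level of significance will be set at 0.05".

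**The concern.** With two active arms and a shared placebo there are two chances to declare that the tablet works. The Sample size section promises a single 5 % error rate. The Statistical analysis section then sets a level for all tests without saying how that 5 % is shared, ordered or gated across the arms. Read plainly, each dose could be tested against placebo at 0.05, and a significant result at either dose could be reported as efficacy.

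The primary efficacy conclusion is at stake. If only one dose came out significant, a reader could not tell from the plan whether the result had been held to a 5 % standard. The choice of which comparison counts would also still be open after the data were seen.

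**Working it through.** **Inputs from the protocol.** Three arms, 1:1:1 (Randomization and blinding). Two-sided 0.05 for all tests (Statistical analysis). Difference 10, SD 18.2, power 80 %, 79 per group, withdrawal 15 %, 92 per group recruited (Sample size). The error rates below are for one score at one visit, under no true effect in any arm.

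**1. The plan's own figure.** Two-group formula, n = 2 (z₀.₉₇₅ + z₀.₈₀)² SD² / difference²:

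2 × (1.960 + 0.842)² × 18.2² / 10² = 52 per group (53 with the t distribution), not 79.

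So 79 does not follow from the stated inputs as a pairwise comparison at 0.05. A t-test at a level of 0.01 gives about 79, but the protocol states no such level, so 79 is not evidence of a planned adjustment either. The step from 79 to 92 is consistent to rounding: 92 × 0.85 = 78.2, so about 78 per group are expected to complete.

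**2. Error if each dose is tested against placebo at 0.05.** With equal arms and a shared control, the two test statistics have correlation 0.5.

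- Either direction: 1 − P(|Z₁| < 1.96, |Z₂| < 1.96) = 0.0907, about 9.1 %.
- Only false claims that a dose beats placebo: 1 − P(Z₁ < 1.96, Z₂ < 1.96) = 0.0454, about 4.5 %, against 2.5 % for one test.

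**3. Error if high versus low dose is also counted as a claim.** The studentized range for three groups at 1.96 × √2 gives 0.122, or 12.2 %.

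**4. Error if an overall three-group F-test at 0.05 must first be significant.** By simulation (400,000 runs, 79 and 92 per group), the error is 4.1–4.2 % for the two dose-placebo tests and 5.0 % for all three pairs.

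**5. Cost of control on the stated inputs.** At 78 per group the standardized difference is 10 / (18.2 × √(2/78)) = 3.43. Power is Φ(3.43 − critical value):

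| Rule | Level per test | Critical value | Power, normal | Power, t-test |
|---|---|---|---|---|
| Unadjusted | 0.05 | 1.960 | 92.9 % | 92.6 % |
| Dunnett, two comparisons | 0.027 | 2.212 | 88.9 % | 88.3 % |
| Bonferroni, two comparisons | 0.025 | 2.241 | 88.3 % | 87.7 % |
| Bonferroni, three pairs | 0.0167 | 2.394 | 85.0 % | 84.3 % |

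For 80 % power, two controlled comparisons need 62 (Dunnett) or 63 (Bonferroni) per group. Three pairs under Bonferroni need 70. All are below 78.

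**The case against.** The strongest reply is that the protocol never says each pair of arms is tested separately at 0.05. The primary test is unnamed. A single three-group test fits the text, and so does such a test followed by pairwise comparisons only if it is significant. With three arms, that gate keeps the error at about 5 % or below. Dunnett, Tukey and gatekeeping procedures can also be run at an overall level of 0.05, so the closing sentence does not rule them out. The document is a journal article, and an SAP that is not shown may settle the contrasts and the adjustment. The stated aim is also worded as exploring efficacy and safety.

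Most of this stands, and it makes the point conditional. It does not remove it. The article does more than stay silent: it fixes a level for all tests, and nothing in it ties that level to an overall test or to a family of comparisons. An overall test alone would also not show which dose, if either, differs from placebo. The Discussion section expects the trial to provide clinical evidence of efficacy, so a significant dose-placebo result would be read as such.

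A reader might infer that the trial carries a 9–12 % chance of a false efficacy claim. The document does not support that, for three reasons:

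- It depends on ungated pairwise testing, which the text permits but does not state.
- The 12.2 % counts high versus low dose, which is not a claim of efficacy over placebo.
- Both figures count errors in either direction, including a dose appearing worse than placebo.

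Nor can the sample size be called a calculation for one pairwise test at 0.05, because 79 does not reproduce as one.

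**Conclusion.** The point holds in conditional form. The protocol states a two-sided 5 % type I error and sets a blanket 0.05 that does not secure it across two doses and a placebo. If both dose-placebo comparisons are run as that rule permits, the family-wise error is about 9.1 % two-sided. The one-directional risk of a false claim of benefit nearly doubles, from 2.5 % to about 4.5 %. The figure of 12.2 % applies only if high versus low dose is treated as a further claim.

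These rates assume no true effect, equal arms, approximately normal test statistics, one score and one visit. They would not apply if an overall test gated the pairwise tests, or if an SAP sets an adjustment; the protocol states neither.

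**What to change.** For the primary outcome, replace the blanket 0.05 in the Statistical analysis section with a rule that holds a two-sided 5 % over the two dose-placebo comparisons. Either of these would do:

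- Dunnett (about 0.027 each) or Bonferroni (0.025 each).
- A pre-specified fixed sequence, with the second comparison tested at 0.05 only if the first is significant at 0.05. The sponsor should choose the order, since the protocol gives neither comparison priority.

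Report high versus low dose as an estimate with its confidence interval and no claim of significance. If an SAP already sets a controlling rule, including an overall test as a gate, align the protocol sentence with it.

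The change takes a sentence or two and, on the protocol's difference and SD, no extra patients. Dunnett or Bonferroni over two comparisons lowers power at 78 per group from about 93 % to about 88 %. Bonferroni over all three pairs lowers it to about 84 %. Both remain above the planned 80 %. A fixed sequence keeps the first comparison at about 93 %, but the second dose cannot be claimed if the first fails.
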